### Statistical Analyses

#### Sample Size

Our aim is to recruit 90 participants in total. Given an attrition rate between 10% and 16% (see [54] for a review), there would be approximately 27 participants per condition. Assuming a significance level of α=.05, a power of 0.80, and a correlation of *r*=.50 between 3 repeated measures, the G*Power 3 software for mixed designs estimates that the sample size will provide sufficient power to detect a small to medium effect (*f*=0.15). Indeed, small to medium effect sizes correspond to those observed with similar training programs in the meta-analysis by Lampit et al [55].

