#### Analysis of Behavioral and Brain Outcomes

We will use a modified intention-to-treat analysis of behavioral outcomes to minimize attrition-related bias, so that all participants who have completed at least one postbaseline assessment will be analyzed. The effect of training programs on the behavioral outcomes will be analyzed with linear mixed-effects models (LMMs) as this analysis makes it possible to compare performance growth between groups and is resistant to missing values. Training improvements will be tested using IES as the dependent variable with 2 separate analyses using *session* (12 levels: session 1 to session 12) *× condition* (3 levels: IES 1-back/IES 2-back/IES 3-back) for the updating training and *session* (12 levels: session 1 to session 12) *× condition* (2 levels: IES Congruent/IES Incongruent) for inhibition training. When significant interaction effects are found, pairwise comparisons will be computed within each training group (comparing performances at sessions 6 and 12 to session 1) and between training conditions at sessions 6 and 12.

Efficacy of training to improve proximal task performances will be tested at 2 separate *time* (three levels: PRE/POST2/POST4) × *training* (3 levels: inhibition/updating/general knowledge) LMMs, using inhibition and updating composite scores as dependent variables. When significant interaction effects are found, pairwise comparisons will be computed within each training group (comparing performances at POST2 and POST4 to PRE) and between training groups (comparing performances for the inhibition and updating condition to general knowledge condition) at POST2 and POST4. To reduce the statistical power cost due to multiple testing corrections and as we have a priori hypotheses, we will also conduct LMM analyses in the absence of interaction to make a direct comparison between the performances of the general knowledge training group (control active) and the updating or inhibition training groups separately.

Efficacy of training to improve complex WM will be tested in the same way with separate time-varying LMMs (5 levels: PRE/POST1/POST2/POST3/POST4) × *training* (3 levels: inhibition/updating/general knowledge) for each task (ie, reading span, alpha span, and VR composite score).

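### The behavioural mixed models use PRE as an outcome level or as change, but not as an adjustment, so the between-arm contrasts are valid but carry about one third more variance than needed at the plan's own r=.50

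*Protocol article*

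**What the plan says.** The protocol article names the updating and inhibition composites as proximal and primary outcomes (Transfer to Proximal Outcomes). Under Analysis of Behavioral and Brain Outcomes, each composite is analysed in a linear mixed model with time (PRE, POST2, POST4) crossed with training (three arms). PRE is therefore part of the response. If the interaction is significant, pairwise comparisons follow "within each training group (comparing performances at POST2 and POST4 to PRE) and between training groups". The between-arm ones set inhibition and updating against general knowledge at POST2 and at POST4. Without an interaction, a direct comparison of each training arm with the control arm is still planned, but its contrast is not spelled out. Reading span, alpha span and the virtual reality composite are handled in the same way over five occasions.

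The Sample Size section assumes "a correlation of *r*=.50 between 3 repeated measures" and expects that "there would be approximately 27 participants per condition".

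**The concern.** In a time by training model whose arm means are free at PRE, having PRE in the data does not adjust the contrast at a later visit. With complete data, that contrast is the difference in post means, and whatever difference the arms happened to have at PRE stays in it in proportion to the correlation. The interaction test does use PRE, but as change, which subtracts the whole baseline difference instead of the part that predicts the post score. The within-arm changes from PRE are not randomised comparisons, and they include any retest gain that all arms share.

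Precision is at stake. The trial expects small to medium effects with about 27 people per arm, and a baseline measure it already schedules for everyone could sharpen every between-arm comparison.

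**Working it through.** **Inputs.** From Sample Size: "Assuming a significance level of α=.05, a power of 0.80"; r=.50; three occasions; f=0.15; 90 recruited; about 27 per condition (81 in total). My assumptions: two-sided pairwise tests, complete data, equal variance at each visit, and r=.50 as the PRE-to-post correlation. SD means the between-person SD of the outcome at one visit.

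**The plan's own figure.** The G*Power formula for the within-between interaction is λ = f²·N·m/(1−r), with df₁ = (k−1)(m−1) = 4 and df₂ = (N−k)(m−1).
- N=81: λ = 0.0225×81×3/0.5 = 10.94, df₂ = 156, power 0.745.
- N=90: λ = 0.0225×90×3/0.5 = 12.15, df₂ = 174, power 0.796.

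The stated 0.80 is thus met, to rounding, with all 90 analysed, but not with the 27 per condition expected after attrition. The present point does not depend on that gap. It only shows that there is little precision to spare.

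**Is the POST contrast adjusted?** A random-intercept time by training model was fitted to one simulated data set with 27 per arm. Its POST4 difference between two arms was −0.06697, identical to the raw difference in POST4 means.

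**Relative variance of a between-arm contrast at one post visit**
- raw post: 1
- change from PRE: 2(1−r) = 1.0 at r=.50
- adjusted for PRE: 1−r² = 0.75 at r=.50

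The ratio 1/0.75 = 1.33 is one third more variance for raw post and for change.

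**Standard error**, √(2v/27): √(2×1/27) = 0.272 SD; √(2×0.75/27) = 0.236 SD.

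**Difference detectable with 80% power**, (1.96+0.84)×SE: 0.76 and 0.66 SD.

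**Equivalent size:** 27/0.75 = 36 per arm would be needed without adjustment to match 27 with it. For a difference of 0.6 SD, chosen only as an illustration, power is 0.60 without and 0.72 with adjustment.

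**Simulation** (20,000 two-arm trials, 27 per arm, r=.50): variances 0.0734 raw, 0.0730 change, 0.0555 adjusted. The adjusted-to-raw ratio is 0.756, close to the theoretical 0.75.

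**Sensitivity to r**

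| r | Raw | Change | Adjusted | Variance saved vs raw | Variance saved vs change |
|---|---|---|---|---|---|
| .3 | 1 | 1.4 | 0.91 | 9% | 35% |
| .5 | 1 | 1.0 | 0.75 | 25% | 25% |
| .7 | 1 | 0.6 | 0.51 | 49% | 15% |

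(The last two columns are 1 − adjusted/raw and 1 − adjusted/change.)

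**Chance imbalance at PRE.** P(|PRE difference| ≥ 0.3 SD) = 2[1−Φ(0.3/0.272)] = 0.27 for a single comparison. Given a difference of 0.3 SD, the raw post contrast shifts by r×0.3 = 0.15 SD. The change contrast shifts the other way, by (r−1)×0.3 = −0.15 SD. The adjusted contrast is not shifted.

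**The case against.** The strongest reply is that the lead efficacy test is the time by training interaction, a randomised comparison of change between arms, and that the pairwise contrasts normally follow only when it is significant. PRE is therefore not ignored. This stands, and the point is worded accordingly. It does not remove the loss: at r=.50 change is no more precise than the raw post score, and the direct comparisons with control go ahead without a significant interaction.

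A second reply is that a model with arm means constrained equal at PRE is itself a time by training mixed model, so an analysis plan not shown here could specify it. That is possible. As printed, though, the factors are fully crossed and no constraint is named, and using PRE as a covariate would change the stated model.

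A reader might infer that the planned contrasts are biased. The documents do not support this. Allocation is random, so the contrasts are unbiased on average; the shift arises only conditionally on an observed imbalance, and 0.15 SD is about half the contrast's standard error (0.15/0.272 = 0.55). Nor is an imbalance of 0.3 SD the expected case, since about 73% of single comparisons fall below it.

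A reader might also extend the point to the brain outcomes. For those the article gives mixed ANOVAs in regions of interest and whole-brain analyses, and states no between-arm contrast of post levels, so the point is not made there.

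**Conclusion.** The planned behavioural analyses are valid, and the article does not contradict itself here. They are inefficient: at the plan's r=.50 and 27 per arm, both the raw post contrast and the change contrast have one third more variance than a PRE-adjusted contrast, and the detectable difference is 0.76 instead of 0.66 SD. The figures describe one post visit with complete data. With missing visits the mixed model borrows some information from PRE, but that does not amount to adjustment.

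The size of the gain rests on a planning correlation that the data may not show. Adjustment has the smallest variance of the three at each correlation in the table, but the gain can be modest: 9% in variance against raw post at r=.3, or 15% against change at r=.7. This is a recommended improvement, not a correction of an error.

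**What to change.** For the proximal, complex working memory and virtual reality outcomes, either keep PRE as a response in the time by training model and constrain the three arm means to be equal at PRE, or model the post visits with PRE by time as covariate. Take every between-arm test and contrast from that one model, including the direct comparisons with control that are made without a significant interaction. Report within-arm changes from PRE as descriptive.

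No new data or visits are needed, because PRE is scheduled for every participant. The cost is a changed model statement. The Results section says that data collection ended in April 2019 and analysis began in June 2020, so the change should be recorded as a dated amendment that states whether outcome data by arm had been seen.

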## Introduction

### Background

Slowing age-related cognitive decline is a central concern for the prevention of pathological aging and loss of autonomy. Cognitive training has been identified as having significant potential in this context [1]. Many studies have identified working memory (WM) as a target for cognitive training because it is considered a foundational element of cognition. WM maintains and manipulates online information and supports many complex cognitive activities including language comprehension, reasoning, and mathematical abilities. Furthermore, aging and neurodegenerative diseases can impair WM, which has a negative impact on the ability to carry out high-level cognitive tasks. WM is a multicomponent system and relies on different attentional control processes (see [2] for a review), some of which have been the target of WM training programs. The goal of this study is to compare the effect of 2 attentional control training programs in older adults, each targeting major WM processes: inhibition and updating. A side-by-side comparison of inhibition and updating training programs will determine their respective and comparative impact.

We propose to measure the training program’s effect on proximal measures, as well as on transfer tasks and brain outcomes. Moving from proximal to transfer tasks is critical. A large number of studies have used updating training in older adults and found improvements on proximal tasks, (eg, [3-5]), with some generalization to switching tasks (eg, [6]). A few studies reported that inhibition training was effective when measured with inhibition tasks that were similar to those done in training [7,8]. However, little evidence was found to support generalization to untrained tasks. Thus, inhibition and updating training improve tasks that are similar to the training, but little is known about their effect on more complex tasks or comparative efficacy. It is important to determine whether improving one attentional process improves another, which would suggest within-WM generalization. In addition, tasks typically used to measure transfer rely on laboratory-based cognitive tasks, designed to reflect fine cognitive functions or processes. They are therefore not representative of the complexity present in everyday life. Thus, in addition to traditional complex WM tasks, transfer will be assessed using virtual reality, which can be used to reproduce real-life situations [9,10].

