### Objectives

The general goal of the study is to compare 2 process-based interventions, inhibition and updating WM training, and assess their effect on the cognition and brain of cognitively healthy older adults relative to an active control condition. There are 6 objectives to the study: (1) measure the gains on the trained tasks; (2) determine transfer of gain on (i) proximal measures that are not trained directly but reflect the trained process, (ii) complex WM measures, and (iii) virtual reality tasks designed to reflect WM in real life; (3) identify the effect of WM training on cortical thickness and task-related brain activation in regions known to be involved in updating or inhibition or both; (4) assess whether cognitive (eg, pretraining cognition), psychosocial (lifestyle, education, motivation), and biological markers (eg, white matter lesions, sex, genotype) moderate the effect of training on cognitive and brain outcomes; (5) examine dose effects by measuring training, transfer, and cerebral outcomes at different time points; and (6) assess if training reduces the age-related deficit on cognitive and cerebral measures.

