### Hypotheses

It is hypothesized that older participants enrolled in WM training will show larger cognitive gains than those in the active control condition, and that gains will be specific to the cognitive process trained. We expect brain changes to be observed in regions that are associated with the trained process, with an overall decrease in activation due to improved neural efficiency for both functional magnetic resonance imaging (fMRI) tasks. It is expected that both trainings improve brain and performance parameters in older adults, which will increase to the levels of younger adults. Finally, it should be possible to identify individual factors that moderate the magnitude of the effect. The intervention may especially benefit participants with less advantageous cognitive and genetic profiles. However, these participants may require additional training for the intervention to be effective [26].

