## Discussion

This study is a randomized double-blind controlled trial designed to examine the impact of 2 attentional control interventions, inhibition and updating, on the cognition and brain of older adults. The effect will be examined on proximal measures of inhibition and updating, complex WM measures and brain status, which will be measured with structural MRI and fMRI. Updating and inhibition are linked to age-related decline in WM [58], and have been identified as the most critical attentional control processes supporting fluid cognition [59]. Some studies have found some cognitive improvements following attentional control training in older adults (see [54] for a review). However, no study has yet to compare the relative efficacy of 2 attentional control interventions in older adults.

One strength of this study is precisely the side-by-side comparison of updating and inhibition interventions, against an active control condition. Moreover, updating and inhibition rely on distinct brain regions (eg, frontostriatal regions and right inferior frontal gyrus, respectively), which simplifies the examination of the relationship between brain and cognitive changes. This study will also establish whether inhibition and updating training programs are useful cognitive interventions to improve performance beyond the training tasks and, ultimately, to improve complex WM functioning in aging. The inclusion of a group of younger adults will help determine whether the training programs increase the performance of older adults to the level of the younger participants. Comparing younger and older adults will also clarify whether cognitive gains result from the restoration of the specialized brain regions (eg, normalization of activations relative to younger adults) or from compensative processes (eg, increased activations in specialized or alternative regions).

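### No planned behavioural contrast isolates inhibition from updating training, and none compares gains across the two composites, although the trial's goal and specificity hypothesis need both

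*Protocol article*

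**What the plan says.** The aim is stated in several places. The Objectives section says: "The general goal of the study is to compare 2 process-based interventions, inhibition and updating WM training", and adds assessment of both relative to an active control. The Background says: "A side-by-side comparison of inhibition and updating training programs will determine their respective and comparative impact". The Hypotheses section expects larger gains than control and that "gains will be specific to the cognitive process trained". The Discussion repeats the claim: "One strength of this study is precisely the side-by-side comparison of updating and inhibition interventions, against an active control condition".

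The section Analysis of Behavioral and Brain Outcomes fits one time × training model to each primary composite ("3 levels: inhibition/updating/general knowledge) LMMs, using inhibition and updating composite scores as dependent variables"). After a significant interaction, the between-arm comparisons are "between training groups (comparing performances for the inhibition and updating condition to general knowledge condition) at POST2 and POST4". Without an interaction, the control arm is compared with the updating arm and with the inhibition arm, each separately. Reading span, alpha span and the VR score are handled in the same way over five time points. For brain outcomes the section names mixed ANOVAs in regions of interest and lists no between-arm contrasts.

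**The concern.** The contrast list is written out twice, once with and once without an interaction, and both times it omits the pair of arms that the trial sets out to compare. Because the two composites sit in separate models, no term sets the gain on the trained process against the gain on the untrained one.

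What would be left is a comparison of significance labels: one training beats the quiz on a composite and the other does not, so the first is called better or process-specific. Two trainings with the same true effect can easily fall on opposite sides of the threshold at this sample size. The headline conclusion on relative efficacy would then have no planned test that isolates it, and a contrast added once results are known would be post hoc.

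**Working it through.** **1. Do other parts of the analysis fill the gap?**
- *Trained-task models.* These include a comparison between training conditions at sessions 6 and 12. They are fitted separately within the updating and the inhibition arm, and condition there means N-back level or congruency. They do not compare arms.
- *Age analysis.* Each arm is compared with the younger adults, not with the other training arm.
- *Omnibus time × training test.* Its null includes equality of the two trainings, but rejection may come wholly from training versus control.

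**2. The plan's own power figure** (Sample Size: 90 recruited, about 27 per arm after attrition, α=.05, r=.50, 3 measures, f=0.15, power 0.80).

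Interaction test with k=3 arms, m=3 measures and sphericity assumed: λ = f²·N·m/(1−r), df = (k−1)(m−1) and (N−k)(m−1).
- N=90: λ = 0.0225×90×3/0.5 = 12.15, df 4 and 174, power 0.796. The figure reproduces on the recruited number.
- N=81 (27 per arm): λ = 10.94, df 4 and 156, power 0.745.

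This power belongs to the omnibus test and says nothing about any pair of arms.

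**3. How often do the listed contrasts disagree when the trainings are equal?**

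Inputs: n=27 per arm and r=.50 (Sample Size). Assumed: the same true gain d in both training arms, baseline adjustment (residual variance 1−r² = 0.75), a normal test at 1.96, and no omnibus gate, since the fallback lets the control comparisons proceed without one.

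Standard error of each contrast = √(2×0.75/27) = 0.236. The two contrasts share the control arm, so they correlate 0.5. With p the chance that one contrast is significant and b the chance that both are, P(exactly one) = 2(p−b). By symmetry, half of that favours each arm.

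| d | p | b | exactly one | favours the arm trained on that process |
|---|---|---|---|---|
| 0.30 | 0.246 | 0.118 | 26% | 13% |
| 0.50 | 0.564 | 0.400 | 33% | 16% |
| 0.65 | 0.788 | 0.670 | 23% | 12% |

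With unadjusted change scores (variance 2(1−r) = 1.0) the exactly-one column is 22%, 33% and 30%. A direct two-sided 5% contrast of the two trainings errs in 5% of such trials, 2.5% in the specificity direction.

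**4. Power of the missing contrast.** For a two-arm difference in change from PRE, the SD of change is √(2(1−.50)) = 1.0 and the standard error with 27 per arm is √(2/27) = 0.272. With a two-sided 5% t test on 52 df:
- power 0.19 at 0.3 SD and 0.44 at 0.5 SD;
- 80% power at 0.78 SD;
- with a Bonferroni correction over three pairwise contrasts (assumed), 80% power at 0.91 SD.

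**The case against.** Four points on the other side carry weight.

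- *A reader might infer that the comparison is never tested.* The document does not support that. All three arms are in each model, equality of the two trainings is part of the omnibus null, and the pair can be estimated from the fitted model. The goal also has two parts, and the listed contrasts do test the half concerning gains over control.
- *Specificity is addressed indirectly.* Each training meets the control on both composites, with within-arm changes alongside. That is evidence of a kind, but it still compares separate significance results.
- *A reader might take the whole 33% as false specificity.* Half of the discordant results run the other way and contradict specificity. The full false pattern, in which each arm is significant only on its own composite, is rarer still: 0.164² = 2.7% at 0.5 SD if the composites are independent. The 0.5 SD case also lies near the peak. If both trainings gain equally and fully by POST2, the design effect f=0.15 corresponds to about 0.68 SD (f = 0.222d). With linear growth to POST4 it is about 0.78 SD. Discordance there is about 21% and 12%, half of it in the favouring direction. These mappings are assumptions.
- *A reader might extend the point to the brain outcomes.* Their between-arm contrasts are not spelled out, and an article may leave them to the analysis plan, so no defect can be asserted there.

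The objection that contrasts are detail for an analysis plan does not stand for the behavioural outcomes. The article fixes the list, and the list does not match the stated goal.

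**Conclusion.** The point holds for the behavioural outcomes, including both primary composites. No planned contrast isolates inhibition from updating, and no planned test compares gains across the composites. The listed comparisons with control remain valid for what they test, but they cannot support a claim that one training is better or that gains are process-specific.

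On size, for equal true gains of 0.3 to 0.65 SD the separate comparisons favour the arm trained on a composite's process in about 12% to 16% of trials, against 2.5% for a direct contrast. This rests on the assumed gains, 27 per arm, r=.50, baseline adjustment and no omnibus gate. It should be corrected before comparative results are reported, since the comparison is central to the stated goal.

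**What to change.** - In each proximal model, add the inhibition-minus-updating contrast of change from PRE at POST4, with POST2 secondary.
- For specificity, fit one joint model of both PRE-standardised composites and test the composite × (updating vs inhibition) contrast of change at POST4.
- Add the same head-to-head contrast to the reading span, alpha span and VR models.
- State that claims of relative efficacy or specificity rest on these contrasts, reported with confidence intervals, and not on separate comparisons with control.
- Date the addition, because data collection ended in April 2019 and analysis began in June 2020.

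The cost is analysis wording and a few lines of code on data already collected. There are two downsides to state. Each outcome gains a contrast in the multiplicity count. Power is also limited: with 27 per arm, 80% is reached only at about 0.78 SD on change scores. Many results will be inconclusive, and a non-significant difference must not be read as equivalence of the two trainings.

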Finally, we will use a per-protocol analysis for the neuroimaging outcomes. Structural MRI images will be analyzed with FreeSurfer 6 [56] to calculate regional cortical gray matter thickness, area, and volume, in the prefrontal, parietal and temporal cortices. Subcortical volumes were segmented for basal ganglia and hippocampi. fMRI images will be preprocessed with SPM12 [57] (realignment, slice timing, coregistration, normalization, smoothing) and will be analyzed as a block design model at subject level with a fixed-effects general linear model (GLM). The GLM will use 1 regressor for each condition task convolved with a canonical hemodynamic response function. A high-pass filter of 128 seconds will be applied to remove low frequencies. Task-related activation will be analyzed using the following fMRI contrasts: [1-back > 0-back] and [2-back > 0-back] as a measure of updating at varying task loads; and [2-back > 1-back] as a measure of load-related activation for the N-back task; [congruent > neutral] as a measure of reading-related activation; and [incongruent > neutral] and [incongruent > congruent] as measures of inhibition for the Stroop task. Whole-brain analysis will help determine task-related activation and whether alternative regions are recruited throughout or after training. Mixed ANOVAs will be carried out in regions of interest using beta weights from the activation clusters and from well-documented task-related regions. We will also adopt a parametric approach analysis, in which the first-level GLM included regressor for task block with parametric modulator for WM load.

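### The brain outcomes of Objective 3 rest on a per-protocol analysis alone, with a complete-case type of model for fMRI regions, while the same participants' behavioural outcomes get modified intention-to-treat and mixed models

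*Protocol article*

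**What the plan says.** All of this stands in the protocol article under Analysis of Behavioral and Brain Outcomes, unless another section is named.

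- **Behavioural outcomes, population.** The approach and its reason are given together: "We will use a modified intention-to-treat analysis of behavioral outcomes to minimize attrition-related bias". The inclusion rule attached to it is that "all participants who have completed at least one postbaseline assessment will be analyzed".
- **Behavioural outcomes, model.** Linear mixed models are chosen because "this analysis makes it possible to compare performance growth between groups and is resistant to missing values".
- **Brain outcomes, population.** "Finally, we will use a per-protocol analysis for the neuroimaging outcomes". No second analysis set is named for them and no reason is given for the change.
- **fMRI, whole brain.** "Whole-brain analysis will help determine task-related activation and whether alternative regions are recruited throughout or after training".
- **fMRI, regions of interest.** "Mixed ANOVAs will be carried out in regions of interest using beta weights from the activation clusters and from well-documented task-related regions".
- **Structural MRI.** FreeSurfer is used "to calculate regional cortical gray matter thickness, area, and volume, in the prefrontal, parietal and temporal cortices", plus basal ganglia and hippocampi. These are named anatomical regions. The ANOVA sentence speaks of beta weights and so does not reach them.
- **Objectives.** Objective 3 asks what training does to cortical thickness and task activation, in regions already known to serve the trained processes.
- **Procedure and Table 1.** Brain outcomes are measured at PRE, POST2 (midway, after session 6) and POST4.
- **Analysis of Dose Effects.** Growth models are planned for behavioural and brain outcomes.

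**The concern.** Objective 3 is a question about the effect of training, and randomisation is what allows it to be answered. A per-protocol set is formed by what happens after randomisation. The three arms did different things (N-back exercises, Stroop-like exercises, a quiz), so equal exclusion across arms cannot be taken for granted. The reason given for modified intention-to-treat applies to the scans as much as to the cognitive tests, since they come from the same people with the same attrition.

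Two further consequences follow. Someone who stops after the POST2 scan has two usable scans. A mixed model would use both, whereas a conventional repeated-measures ANOVA over three visits uses neither. In addition, brain and behaviour results would describe different samples, although the Discussion counts relating brain change to cognitive change among the design's advantages.

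A separate question arises for fMRI. Some regions of interest come from activation clusters, and the whole-brain analysis that precedes them looks in part for regions recruited during or after training. If clusters are picked because they show training-related change, testing that same change in them is circular.

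**Working it through.** **1. The plan's own figure, and what fewer analysed participants would cost.** Inputs from Sample Size: 90 recruited, attrition 10% to 16%, α = .05, power 0.80, r = .50, three measures, f = 0.15. There are three arms. The section does not say which mixed-design test was meant; the group-by-time interaction is the one that matters here.

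λ = f²·N·m/(1 − r), df1 = (3 − 1)(3 − 1) = 4, df2 = (N − 3)(3 − 1)

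| N analysed | Basis | λ | df2 | Power | f detectable at 80% |
|---|---|---|---|---|---|
| 90 | all recruited | 0.0225 × 90 × 3/0.5 = 12.15 | 174 | 0.796 | 0.151 |
| 81 | 10% loss | 10.94 | 156 | 0.745 | 0.160 |
| 76 | 16% loss (90 × 0.84 = 75.6) | 10.26 | 146 | 0.713 | 0.165 |
| 66 | assumed further exclusions, 22 per arm | 8.91 | 126 | 0.640 | 0.177 |

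The stated 0.80 is reproduced for the interaction at N = 90. That it holds only before attrition is a different matter and is not argued here. The rows show only that each scan set left out has a price.

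**2. Possible bias from per-protocol exclusion.** Assume that the lowest fraction q on some trait is excluded from one arm only, and that the trait correlates ρ with the outcome. The spurious difference in SD units is ρ·φ(z_q)/(1 − q).

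- q = 0.10: φ/(1 − q) = 0.195, giving 0.04 (ρ = 0.2) to 0.10 (ρ = 0.5).
- q = 0.16: φ/(1 − q) = 0.290, giving 0.06 (ρ = 0.2) to 0.14 (ρ = 0.5).

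Only the 10% and 16% come from the document, and there they are overall attrition rates. The one-arm exclusion and the correlations are assumptions. Exclusion of the same kind in every arm would largely cancel.

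**3. Selecting fMRI clusters.** Null simulation: no true group-by-change effect, 27 per arm, independent candidate clusters, 2,000 runs, nominal 5%. One cluster is selected and the group difference in change is then tested in it.

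| Selection rule | 5 clusters | 10 clusters | 20 clusters |
|---|---|---|---|
| Largest group-by-change effect | 24% | 40% | 65% |
| Task effect pooled over arms and visits | 5% | 4% | 5% |
| Post-training activation in one arm | 6% | 7% | 8% |

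The first row agrees with 1 − 0.95^k = 23%, 40% and 64%. Whether the test is valid therefore depends on the selecting contrast, which the article does not state.

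**The case against.** Several points on the other side stand.

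- **A reader might infer that Objective 3 loses its randomised comparison.** It does not. The three randomised arms can still be compared within the per-protocol set. Nor is the behavioural side a full intention-to-treat analysis: participants without a post-baseline assessment drop out, and the trained-task models contain no between-arm term.
- **A reader might equate the per-protocol set with people who completed training.** The article does not define the set, and it could mean little more than having usable scans. The definition may properly sit in a fuller document, so its absence is not the complaint. The stated choice of per-protocol, with no counterpart, is.
- **A reader might take the whole of Objective 3 to be ANOVA-based.** The ANOVA and cluster sentence concerns fMRI beta weights only, not cortical thickness or volume. Growth models for brain outcomes are also planned, but they serve the dose question and are not offered as the efficacy analysis.
- **A reader might infer that the region-of-interest test is circular.** The article does not support that as a flat statement. The listed contrasts are within-person task contrasts, well-documented regions are used alongside the clusters, and selection on a pooled task effect keeps the error near 5%. The point is conditional. It is not idle, though, because the whole-brain aim includes regions recruited through training.
- **The primary outcomes are the cognitive composites**, so the main efficacy conclusion is untouched.

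What the objection does not answer is why attrition bias should be guarded against for cognition and not for the brain.

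**Conclusion.** The concern holds in limited form. For brain outcomes the plan states a per-protocol analysis only and, for fMRI regions, a model that conventionally needs all three scans. For behaviour in the same participants it adopts an approach chosen to limit attrition bias and tolerate missing visits. The randomised comparison for Objective 3 is weakened by an amount that cannot be derived from the document. The 0.04 to 0.14 SD range illustrates selective exclusion in a single arm and is not an estimate for this trial. The power figures likewise show only the direction and rough cost of discarding scans, since no scan-completion counts are given.

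The per-protocol point covers thickness, volume and activation. The ANOVA and cluster points cover activation only. Circularity arises only if clusters are selected on the effect being tested; the remedy there is to fix the selecting contrast. The change is worth making because Objective 3 is one of six stated objectives, but it does not bear on the primary cognitive outcomes.

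**What to change.** 1. Make the main analysis of region-of-interest betas, thickness and volumes a time (PRE, POST2, POST4) by training linear mixed model in all randomised older participants with at least one usable post-baseline scan, analysed as randomised. This parallels the behavioural rule, although the two samples may still differ by those with tests but no scan.
2. Keep the per-protocol analysis as a sensitivity analysis.
3. For fMRI, base inference on training-by-time effects on the a priori task-related regions, or on clusters selected by a contrast independent of that test. One example is the task effect in PRE scans pooled over arms. That choice protects the comparison between arms. It does not protect change from PRE within one arm, because regions picked for high PRE values tend to fall back.
4. Report clusters found from training-related change as descriptive.

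The cost is wording and refitting, and no new scans are needed. Participants with a low training dose will dilute the estimate slightly, but the per-protocol result remains to show by how much. Since the Results section says that analysis began in June 2020, the change should be dated and marked as made before or after the brain results by arm were seen.
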